### Interim analyses {21b}

Two ‘formal interim analysis’ meetings will be held by the Data and Safety Monitoring Board (DSMB) by teleconference (or face-to-face, if possible) to review the data relating to treatment efficacy, patient safety and quality of trial conduct.

A recommendation to discontinue ATOCH-II prematurely will be based upon there being clear evidence that the treatment provides protection or causes harm for an important clinical outcome.

### Methods for additional analyses {20b}

Subgroup analysis of haematoma volume and age was planned to be conducted.

### Methods in analysis to handle protocol non-adherence and any statistical methods to handle missing data {20c}

The full analysis set (FAS) included the patients who took the drug at least once and had the primary therapeutic evaluation data at baseline. In the FAS, missing data from the 4 weeks of treatment were replaced with the last available data, in accordance with the last observation carried forward (LOCF) principle. If more than 5% of patients have a missing primary outcome, we will use multiple imputations for a sensitivity analysis.

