#### Relevant concomitant care permitted or prohibited during the trial {11d}

Most participants are treated as outpatients receiving conventional and standard cares such as rest and pain relief. Family members are responsible for monitoring the patients for progress in neurological symptoms such as worsening headaches. If a patient is reported to have worsening symptoms, he or she will be further evaluated by two attending physicians for neurological deficits. These patients may be admitted during the trial for the treatment of progressing neurological deficits and discharged when their symptoms are relieved significantly.

Within 72 h prior to treatment, CT, routine blood test, coagulation, blood glucose and biochemical analysis were rechecked before enrolling into the group, as well as neurological assessment. At the end of 2 weeks and 4 weeks, routinely check blood test, coagulation, blood glucose and biochemical analysis and re-evaluate neurological function. CT scans are performed at end of 2 weeks, 4 weeks and 3 months. mRS and ADL-BI were scored before treatment and at the end of 4 weeks, 3 months and 6 months.

Each patient receives an in-person clinical assessment at an outpatient clinic by two attending neurosurgeons who are kept blind to the treatment allocation, every 2 weeks during the 28-day treatment duration, and then each month thereafter until 180 days post-randomization.

Anticoagulants (warfarin or new oral anticoagulants) are prohibited. Antiplatelet drugs (aspirin, clopidogrel) or Xuesaitong (traditional Chinese medicine for activating blood circulation) can potentially interfere with haematoma absorption and are not recommended during the treatment. However, these patients will not be exclusively excluded from the trial participation. The following drugs may potentially interact with statins and/or cause adverse events and will not be recommended during the treatment: red yeast rice, erythromycin, fibrates, cyclosporin, macrolide antibacterials, azole anti-fungals, tacrolimus, gemfibrozil, troglitazone and itraconazole.

The use of other medications is recorded in the case report form (CRF), including their name, dose and duration of treatment. Any change in haematological and biochemical markers, such as liver function tests, and side effects, such as myalgia, constipation and other possible drug-related symptoms, will be recorded. All details of any treatment during the 180-day study period are recorded.

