### Outcomes {12}

The primary outcome is a composite of ‘good outcome’, including any reduction in subdural haematoma volume from baseline and free of surgery and death within 28 days of the treatment. The haematoma volume is measured centrally using the Tada formula of maximal length (L) × maximal width (W) × maximal thickness (H), divided by 2 [23], on the acquired CT images by 3 independent neuroradiologists blind to the treatment location. Details of the location, density and compartment of the haematoma are also recorded.

Secondary outcomes include functional outcome according to a ‘shift’ in the distribution of the full range of scores on mRS at 28 days; function on the modified Barthel Index measure of actives of daily living (ADL-BI) at 28 days; surgical intervention at 28, 90 and 180 days; and reduction in haematoma volume at 14, 28 and 90 days.

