### Sample size {14}

We estimate a sample size of 240 patients will provide 90% power to detect a treatment effect of 20% absolute improvement in the primary composite good outcome, after considering a 5% loss-to-follow-up at 4 weeks, then 240 patients in total with 120 per group is needed to be recruited for this study and good outcome in the single atorvastatin control group of 62.6% being consistent with the single atorvastatin group of the ATOCH trial (48 of 81) [15], a pilot trial showing 20 of 30 patients had a good outcome in a single atorvastatin group [23] and medical record data showing 9 of 12 patients had a good outcome at a single centre in 2017 [17]. The combined drug treatment effect was assumed to be consistent with the percentage of good outcomes found in 29 of 30 patients in a pilot clinical trial [23] and 95 of 108 patients’ medical records from our single centre showing a good outcome.

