## Statistics methods

### Statistical methods for primary and secondary outcomes {20a}

The primary analysis will be performed according to the intention-to-treat (ITT) principle, comprising all randomized participants. A per-protocol analysis will also be undertaken for all participants who have taken at least one dose of the trial medication and complete at least one follow-up assessment. The description of indicators will be by number of cases (and percentages) for categorical variables, and mean (standard deviation) or median (interquartile range) for continuous variables. The chi-square test and logistic regression with adjustment for site, age, sex and baseline haematoma volume will be adopted for the comparison of the primary outcome between the treatment groups. For secondary outcomes, Student’s *t*-test or non-parametric Wilcoxon tests will be performed for continuous outcomes and the chi-square test for dichotomous outcomes. Ordinal logistic regression will be used for the analysis of the shift in the full range of scores on the mRS. All statistical tests are two-sided, with a *p*-value < 0.05 indicating statistical significance. All analysis will be conducted using SAS 9.4 (SAS Institute Inc., USA).

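### Last observation carried forward scores a lost patient's 28-day composite by when the patient left, and the only check on it is not triggered at the planned 5% loss

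*Protocol article*

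**What the plan says.** All references are to the protocol article.

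- **Missing-data rule.** The section on non-adherence and missing data {20c} states that, in the FAS, "missing data from the 4 weeks of treatment were replaced with the last available data", and names the LOCF principle. The FAS consists of "patients who took the drug at least once and had the primary therapeutic evaluation data at baseline", so no post-baseline observation is needed to be in it.
- **Sensitivity analysis.** The same section adds: "If more than 5% of patients have a missing primary outcome, we will use multiple imputations for a sensitivity analysis".
- **Primary outcome.** Outcomes {12} defines a good outcome as "any reduction in subdural haematoma volume from baseline and free of surgery and death within 28 days of the treatment".
- **Primary population.** Statistical methods {20a} says: "The primary analysis will be performed according to the intention-to-treat (ITT) principle, comprising all randomized participants". It gives no rule for a missing outcome and does not say how this population relates to the FAS.
- **CT schedule.** The concomitant care section {11d} says that "CT scans are performed at end of 2 weeks, 4 weeks and 3 months". Table 1 agrees: haematoma volume is taken at screening and at days 14, 28 and 90.
- **Planning assumptions.** Sample size {14} gives "good outcome in the single atorvastatin control group of 62.6"%, a 20-point absolute improvement and 240 patients, "after considering a 5% loss-to-follow-up at 4 weeks".

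**The concern.** LOCF suits this endpoint badly. Freedom from surgery and death over 28 days is a statement about the whole period, and a day-14 status cannot settle it. For a patient who is truly lost, the only volume available to carry is the day-14 or the baseline value. The filled-in result then reflects the time of departure, not the outcome at day 28. The filled values are also treated as observed, so the analysis understates its own uncertainty.

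The safeguard does not close the gap. The alternative analysis is conditional on more than 5% missing, which is the loss the plan already expects, and it never replaces LOCF as the main analysis. The primary comparison could therefore rest on LOCF with nothing in the plan to test it.

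**Working it through.** **1. The plan's own figures.** The control rate is the pooled result of the three sources cited: (48 + 20 + 9)/(81 + 30 + 12) = 77/123 = 62.6%. Adding 20 points gives 82.6%. With two-sided alpha 0.05, 90% power and a continuity correction, the requirement is 113 per arm. Then 113/0.95 = 118.9, rounded up to 119 per arm or 238 in total, against 240 stated. These inputs are therefore used below. The missing-data point does not alter the sample size.

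**2. How LOCF scores a lost patient** (no contact after the last visit shown):

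| Last information | Value carried to day 28 | Score |
|---|---|---|
| Baseline only, lost before day 14 | Baseline volume, change 0 | Not good |
| Day-14 CT, no reduction | No reduction | Not good |
| Surgery already recorded | Surgery | Not good |
| Day-14 CT, any reduction, no surgery | Reduced, unoperated, alive | Good, with days 15 to 28 unobserved |

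Errors can go both ways. The last row can hide later surgery, death or re-expansion; the first two can hide a later reduction.

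**3. Bias formula.** For arm i let m be the share lost, g the share of those scored good by LOCF, and t the share of them truly good. Then

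bias in the risk difference = m1(g1 − t1) − m0(g0 − t0), where 1 is the dexamethasone arm and 0 is control.

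**4. Planned loss, 6 of 120 per arm** (m = 0.05). Assume that lost patients have the planned arm-specific rates, t1 = 0.826 and t0 = 0.626. The retained patients contribute 0.95 × 82.6 = 78.5 and 0.95 × 62.6 = 59.5 points; lost patients scored good add up to 5.0 points to an arm.

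| Lost patients scored good | Dexamethasone | Control | Difference |
|---|---|---|---|
| All, both arms | 83.5% | 64.5% | 19.0 |
| None, either arm | 78.5% | 59.5% | 19.0 |
| Dexamethasone arm only | 83.5% | 59.5% | 24.0 |
| Control arm only | 78.5% | 64.5% | 14.0 |

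With any common g, the bias is −0.05 × (0.826 − 0.626) = −0.010, that is 1 point toward zero. The values 14 and 24 are arithmetic limits, not expectations.

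**5. Unequal loss, as an assumption.** With the same scoring rule in both arms (all good or all not good), 3 lost on dexamethasone and 9 on control give a difference of 17.6 to 22.6 points; 9 and 3 give 15.4 to 20.4.

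**6. The multiple-imputation trigger.** 5% of 240 is 12, so at least 13 missing outcomes are needed. If each outcome is missing independently with probability 0.05, P(X > 12) = 0.424. At exactly the planned loss the trigger is not met. The text also does not say whether a patient filled by LOCF counts as missing for this purpose.

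**7. Understated uncertainty.** If 12 of 240 outcomes are filled and treated as observed, the ratio of standard errors is roughly √(228/240) = 0.975. This takes the proportions as unchanged and gives no credit for information in the day-14 scan, so about 2.5% is a rough upper figure at the planned loss.

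**8. Secondary outcome.** Table 1 has mRS at screening and then at day 28. Carrying the last value forward therefore imputes no change from screening.

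**The case against.** The strongest points on the other side are these.

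- **Status will often be known.** The adherence section {11c} has patients returning packages weekly until treatment ends, and Table 1 records surgery and adverse events at days 28, 90 and 180. A patient who only misses the day-28 CT may have known surgery and survival status, and nothing in {20c} says that a carried-forward scan overrides a known operation or death. This stands. It confines the problem of unknown surgery and survival to patients with no contact after their last scan. The plan should still say that later information takes precedence, because {20c} does not.
- **LOCF is stated for the FAS, not for the ITT analysis.** This also stands as a matter of text: the link to the primary analysis is an inference. But {20a} offers no other way to score a missing outcome for all randomized participants, so the two sections need reconciling.
- **If the trigger is not met, at most 12 outcomes are missing.** True, and the likely effect is then small. Small is not the same as tested, and the check costs little.
- **Multiple imputation assumes missing at random.** It does not by itself remove bias from loss related to deterioration. This stands, and is the reason for adding a tipping-point analysis.

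A reader might go further and infer that LOCF favours dexamethasone. For example, with 8% lost on dexamethasone and 2% on control, all after day 14, 80% of them reduced at day 14 and a true success share q of 0 to 50%, the bias is (0.08 − 0.02) × (0.8 − q), or +4.8 to +1.8 points. The documents support none of those inputs. Reversing the split gives −4.8 to −1.8. Keeping 8% and 2% but using the planned success rates gives 0.08 × (0.8 − 0.826) − 0.02 × (0.8 − 0.626) = −0.56 points. No direction can be claimed.

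**Conclusion.** The concern holds in a limited form. The protocol states a rule that can score the primary endpoint wrongly for patients who are truly lost, and its only check on that rule is not triggered at the loss the plan expects. The direction of bias is not fixed. At balanced 5% loss and the planned rates the shift is about 1 point toward zero on a 20-point effect, with arithmetic limits of 14 and 24 points if scoring differs fully by arm. These figures assume that lost patients share the planned success rates of their arm; unequal loss changes them.

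The rule should be changed before unblinding. The documents do not support the stronger conclusions that the primary result will be materially biased, or biased in favour of the combination.

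**What to change.** Replace the missing-data text in {20c} and align it with {20a}:

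1. Define one primary population, all randomized participants, and say how the FAS relates to it.
2. Score surgery or death known from any source to have occurred by day 28 as failure, whether or not a CT exists.
3. For outcomes that remain missing, make multiple imputation the main analysis. Use arm, baseline and day-14 volume, age and sex, with site (14 centres) entered simply enough for a stable fit. Derive the composite from the imputed components.
4. Remove the 5% trigger.
5. Keep LOCF as a sensitivity analysis, and add a tipping-point analysis by arm for loss related to outcome.
6. As a secondary point, do not carry the screening mRS forward to day 28.

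No new data are needed. The cost is revised wording, a little more programming and a slightly wider confidence interval: at the planned loss, roughly 1/0.975 = 1.026 times the LOCF width at most, on the same rough basis as step 7 of the working.

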### Plans to give access to the full protocol, participant level-data and statistical code {31c}

Datasets generated and/or analysed will be available to all study investigators, and to investigators at other institutions around the world, according to a data sharing agreement. Data sharing will be available from 12 months after the publication of the main results. We will use Research Manager (ResMan), an Internet-based public platform for clinical research electronic management (http://www.medresman.org.cn/login.aspx), for data sharing.

### Oversight and monitoring

#### Composition of the coordinating centre and trial steering committee {5d}

This trial was managed and operated by the clinical operations department of Beijing Stemexcel Technology Co., Ltd. One project manager was assigned to be responsible for the daily management of the trial, and one CRA was assigned to each participating hospital (some CRAS may be responsible for multiple participating hospitals at the same time). CRA comes to the hospital for clinical supervision once in 2 months.

Data management services are provided by the data department of Beijing Stemexcel Technology Co., Ltd. One data management manager is responsible for the daily management of trial data. At the same time, 2 database technicians are equipped to be responsible for the daily maintenance of the EDC database. Beijing SiteRegular Medical Technology Co., Ltd. provided the Clinical Research Coordinate (CRC) service for this trial. Each participating hospital was assigned a Clinical Research Coordinator (CRC), who was responsible for assisting researchers to complete various Research contents. The above members are responsible for the daily operation of the trial, and the team will hold online project meetings with the sponsor once in 2 weeks. An independent Data & Safety Monitoring Board (DSMB) regularly evaluates the progress of the clinical trial. In addition to the DSMB kick-off meeting, DSMB will convene meetings according to the following frequency: after 50% of the subjects (120 cases) are enrolled and safety observation is completed and after 75% of the subjects (180 cases) are enrolled and safety observation is completed.

### Composition of the data monitoring committee, its role and reporting structure {21a}

The project has an independent DSMB, consisting of a chair, a statistician and a clinical expert, that regularly evaluates the progress of the clinical trial, safety data and important efficacy endpoints and recommends to the sponsor whether to continue, adjust or stop the trial. All DSMB members are independent of the sponsor, DSMB members will disclose all potential conflicts of interest to the sponsor, and there are no financial interests that can influence the decision of the DSMB. The DSMB is governed by a charter outlining responsibilities, procedures and confidentiality and reviews the accumulating unblinded data at regular intervals (Additional file 1: Appendix 1).

### SAE reporting and harms {22}

A serious adverse event (SAE) is defined as an event causing or with potential to cause significant harm or requiring medical intervention, whether or not it is considered related to the study treatment. A non-serious adverse event is defined as any undesirable medical experience occurring to a patient, including abnormal laboratory values without clinical consequences.

All SAEs are to be reported within 24 h of the site investigator becoming aware, and a full report is to be filled to the sponsor and the state food and drug administration (SFDA). The ethics committee of pharmaceutical affairs of ONET will conduct an investigation to confirm the causes of an SAE, decide whether the participant can continue with the study medication and deal with the related participants’ complications and adverse events. All patients are to be followed up according to the intention-to-treat principle. The SAE should be documented in the medical records or patient file and signed and dated by the investigator, for audit and monitoring. Safety outcomes are reported to the presiding Ethics Committees in line with their requirements every 6 months, as well as for review by the DMSB at each meeting.

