### Participant timeline {13}

Baseline demographic and clinical features, including medical history, severity and type of neurological deficit and physical and biochemical results, are collected at the time of enrolment in the study. Treatment should be initiated immediately after randomization (Table 1). All background care should follow standard guideline recommendations for the management of CSDH in China which includes the withholding of anticoagulation and use of antiplatelet agents and prescribing prophylactic antiepileptic drugs and regular use analgesics. Protocol-mandated assessments will be performed according to the schedule (Table 1), and the study flow chart illustrates key steps in the trial (Fig. 1).

**Table 1 Tab1:** Visit and assessment schedule

Items	Screen	Day 1	Day 7 ± 1	Day 14 ± 1	Day 28 ± 3	Day 90 ± 7	Day 180 ± 7
Informed consent	×						
Inclusion/exclusion^a^	×						
Filling general information	×						
Collect medical history	×						
Concomitant medications^b^	×	×	×	×	×		
Physical examination	×						
Surgery		×	×	×	×	×	×
Neurological symptoms^c^	×	×	×	×	×	×	×
Haematoma volume^c^	×			×	×	×	
mRS^c^	×				×	×	×
ADL-BI					×	×	×
Blood routine	×	×		×	×		
Biochemistry	×	×		×	×		
Coagulation	×	×		×	×		
Vital signs^c^	×	×	×	×	×		
Electrocardiography	×			×	×		
Adverse events		×	×	×	×	×	×
Allocate random number	×						
Drug recycling^d^	×	×	×	×	×		

*ADL-BI* activities of daily life on the Barthel Index, *mRS* modified Rankin scale

^a^Accreditation of laboratory examination within 3 days, including head CT, before enrolment

^b^Combined use of drugs before commencing study treatment and continue until the end of the 28-day treatment period

^c^During conservative treatment, if a participant’s neurological function deteriorates associated with an increase in the size of the haematoma and risk of cerebral herniation, they must change over to surgical treatment

^d^Remaining drugs are to be recycled

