### Procedures for unblinding if needed {17b}

All serious adverse events (SAEs) are to be reported within 24 h of the site investigator becoming aware, and a full report is to be filled to the sponsor and the State Food and Drug Administration (SFDA). The ethics committee of the pharmaceutical affairs of ONET will conduct an investigation to confirm the causes of an SAE, decide whether the participant can continue with study medication and whether the need to apply to the organization for emergency unblinding.

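### The SAE definition makes any treated adverse event serious and the non-serious definition excludes nothing, so the serious/non-serious split is unreliable as written

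*Protocol article*

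**What the plan says.** The section on SAE reporting and harms {22} gives both definitions in consecutive sentences. In the first, an SAE is "defined as an event causing or with potential to cause significant harm or requiring medical intervention". It applies whether or not the event is thought to be related to treatment. The second reads: "A non-serious adverse event is defined as any undesirable medical experience occurring to a patient, including abnormal laboratory values without clinical consequences". I found no narrower seriousness criterion and no severity grading elsewhere in the article.

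SAE status has consequences. The same section states: "All SAEs are to be reported within 24 h of the site investigator becoming aware", and adds a full report to the sponsor and the regulator. The section on unblinding {17b} has a committee investigate the cause and "decide whether the participant can continue with study medication and whether the need to apply to the organization for emergency unblinding". Safety outcomes also go to the ethics committees every six months and to the DSMB at each meeting.

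**The concern.** The three alternatives in the SAE definition are joined by 'or', so the third is enough alone: treatment makes an event serious, however mild it is. The second definition covers every adverse event, so an SAE also fits the non-serious wording. Two investigators could file the same treated complaint in different classes, and both would be following the text.

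Treated minor complaints are to be expected. The section on concomitant care {11d} asks sites to record myalgia, constipation and other possibly drug-related symptoms. At the other end, surgery for the haematoma is a component of the primary outcome (Outcomes {12}) and is also a medical intervention. The deterioration leading to it therefore meets the SAE wording, and the article does not say whether that is intended.

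Safety is a stated aim of the trial. If sites apply the wording literally, SAE counts mix serious harm with treated minor complaints, and a real difference between arms is diluted. If sites apply their own judgement instead, the threshold may vary across the 14 centres. Minor complaints would also enter a review process meant for serious events.

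**Working it through.** **Step 1: the two definitions applied to the same events**

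| Event | Meets SAE wording? | Meets non-serious wording? |
|---|---|---|
| Constipation or myalgia, treated | Yes, through the third alternative | Yes |
| Constipation or myalgia, not treated, no potential for significant harm | No | Yes |
| Event causing significant harm | Yes, through the first alternative | Yes, because nothing is excluded |
| Deterioration leading to surgery for the haematoma | Yes, through the third alternative at least | Yes |

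The SAE class is too wide and the two classes are not exclusive. The error is one of over-inclusion: no event causing significant harm is left out.

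**Step 2: illustration of the dilution**

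The document states no SAE rate, so there is no figure of its own to reproduce. From the document: 120 per arm (Sample size {14}) and a two-sided 5% level (Statistical methods {20a}). Assumed:

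- truly serious events in p = 5% of one arm and 15% of the other;
- a share b of each arm that also qualifies through a minor treated event, equal in both arms and independent of serious events.

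Observed SAE proportion in an arm: q = 1 − (1 − p)(1 − b).

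Power = Φ[(|q₂ − q₁| − 1.96·se₀)/se₁], where se₀ = √(2·q̄(1 − q̄)/120), se₁ = √((q₁(1 − q₁) + q₂(1 − q₂))/120) and q̄ is the mean of q₁ and q₂.

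With b = 0: q̄ = 0.10, se₀ = √(2 × 0.09/120) = 0.0387 and se₁ = √((0.0475 + 0.1275)/120) = 0.0382. Power = Φ[(0.10 − 0.0759)/0.0382] = Φ(0.63) = 74%.

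With b = 20%: q₁ = 1 − 0.95 × 0.8 = 0.24 and q₂ = 1 − 0.85 × 0.8 = 0.32. The difference shrinks from 10 to 8 points while the variance rises.

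| b added in each arm | SAE proportions | Risk ratio | Power |
|---|---|---|---|
| 0% | 5.0% v 15.0% | 3.00 | 74% |
| 10% | 14.5% v 23.5% | 1.62 | 43% |
| 20% | 24.0% v 32.0% | 1.33 | 28% |
| 50% | 52.5% v 57.5% | 1.10 | 12% |

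A second assumed pair, 3% v 12%, behaves in the same way: power is 76% with nothing added, 39% with 10% added and 25% with 20% added.

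**The case against.** Several points on the other side stand, and they limit the concern.

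- **Serious events can still be identified.** A reader might infer that serious harm could never be separated from treated complaints. The document does not support that. Side effects, laboratory changes, other medication with dose and duration, and treatment details are all recorded ({11d}), and Table 1 schedules adverse events at each visit from day 1. The defect lies in the labels, and events can be relabelled.
- **The DSMB is not confined to the SAE label.** A reader might infer that a real excess would be hidden from it. The article gives the DSMB safety data, important efficacy endpoints and accumulating unblinded data ({21a}), and ties early stopping to an important clinical outcome ({21b}).
- **Unblinding is discretionary.** The committee decides "whether the need to apply to the organization for emergency unblinding". Nothing shows that a minor complaint would end treatment or break the blind.
- **Background analgesia is a weak example.** Usual care includes "prescribing prophylactic antiepileptic drugs and regular use analgesics". Planned treatment of the haematoma's own symptoms is not clearly an adverse event, so a new treated constipation or myalgia is the better test of the wording.
- **The rates are assumed.** Nothing in the document shows that most patients would have an SAE. The article names no test of SAE incidence and does not power the trial for safety.

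Two objections do not remove the point. It can be said that non-serious plainly means the remainder, and nobody would file a death there. That is true of extreme cases, but it does not settle treated minor ones, because the SAE wording already claims them. It can also be said that an article leaves an itemised seriousness list to the full protocol. A missing list would indeed be no finding, but here a rule is stated, and stated too widely.

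**Conclusion.** The point holds as a defect in a stated definition that should be corrected. As written, treatment alone makes an adverse event serious and the two classes overlap. An SAE comparison built on these labels would be diluted, or would depend on how each centre reads the wording.

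The size cannot be known from the document. The fall in power from 74% to 43%, 28% or 12% is an illustration. It rests on assumed serious-event rates of 5% v 15%, and on minor treated events that are equally common in both arms and independent of serious ones. It shows that a modest admixture matters; it does not estimate what will happen in this trial. If treated minor events differed between arms, the SAE contrast would partly reflect those events instead.

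The primary efficacy analysis is not affected, and the problem can be repaired from the event-level records.

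**What to change.** 1. Remove the unqualified alternative that rests on medical intervention alone. Define an SAE by the seriousness of its outcome, consistent with the GCP principles that the protocol says it follows (section {26b}).
2. Define a non-serious adverse event as every adverse event that does not meet the SAE definition, so that the classes are exclusive.
3. State whether surgery for the haematoma, or the deterioration leading to it, counts as an SAE, given that surgery is part of the primary outcome.
4. Recode the events already reported under the new definition, with treatment allocation still masked to those who recode.

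The cost is a wording amendment with ethics approval and a small recoding task. The article reports 141 of 240 patients enrolled at its last status date, so the amended wording could still cover the reports from later patients. No change to the sample size, the primary outcome or the efficacy analysis is needed.
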